#### Covariates

Each site will define covariates that are appropriate in the context of their electronic health record database. A pre-specified minimum list of potential confounders will be adjusted for. Exploratory modelling will include adjusting for additional confounders that may be available in specific databases.

The confounders to be adjusted for in each database are as follows:

Age on index dateSexDiagnosis of hypertensionDiagnosis of atrial fibrillationDiagnosis of diabetesDiagnosis of dyslipidaemiaDiagnosis of obesitySmoking status, or prescription for nicotine replacement therapy or diagnosis of chronic obstructive pulmonary disease (COPD)Alcohol use (where available) or diagnosis of chronic liver diseaseDiagnosis of rheumatoid arthritis or systemic lupus erythematosusDiagnosis of mental illness (for example, depression, anxiety, bipolar, and/or schizophrenia)Prescription for any antihypertensive medication (for example, angiotensin converting enzyme inhibitors, angiotensin II receptor blockers, calcium channel blocker, beta-blocker, and/or diuretic)Prescription for antidiabetic drugPrescription for antiplatelet agentsPrescription for oral anticoagulants.

Additional confounders that may be adjusted for subject to data source availability:

Deprivation indexBaseline systolic and diastolic blood pressureBaseline body mass indexFamily history of CVD.

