## Introduction

CVD is the leading cause of death globally.^1^ Atherogenic lipoproteins (LDL-C and non-HDL-C) are well-established risk factors for atherosclerotic CVD.^2,3^ Recent evidence from secondary prevention trials indicates that individuals with lower LDL-C concentrations have a reduced risk of subsequent cardiovascular events.^4,5^

While lower targets for LDL-C are gaining wider acceptance for secondary prevention of CVD, there remains limited evidence for specific lipid targets for primary prevention. The recent European clinical guidelines for the treatment of dyslipidaemia emphasise specific LDL-C and non-HDL-C targets for primary prevention according to level of CVD risk.^6^ However, whether achieving a specific lipid target while taking statin therapy for primary prevention corresponds to a reduction in cardiovascular events is uncertain, as most randomised controlled trials of statin therapy have not allocated patients to specific lipid targets. It is also unknown whether there is a lipid level threshold, below which no added clinical benefit is obtained, and if a 'lower is better' approach is appropriate for primary prevention of CVD. Understanding the lowest absolute beneficial level of LDL-C is important as very-low LDL-C levels are now achievable with proprotein convertase subtilisin-kexin type nine inhibitors, and emerging treatments such as inclisiran.^4,7^ The association between on-treatment cholesterol levels and risk of cardiovascular events has been assessed, but these have mostly been in secondary prevention statin trials, and whether these findings extend to clinical practice marked by individual variability in statin response requires further investigation.^8^

Ethnic group, and consequently pharmacogenomics, influences response to statin therapy, particularly for Asians.^9^ Variability in statin response may be present for other non-Caucasian ethnic groups. Moreover, organisation of health systems,^10^ statin dosing,^11^ and individual response to treatment^12^ vary and may impact the magnitude of benefit derived from statin therapy. Given these factors, an assessment of lipid levels in diverse populations is needed to provide representative data, as most primary prevention statin trials enrolled middle-aged Caucasians.^13^ Therefore, this study has two objectives:

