#### Statistical analysis

Descriptive statistics will be used to characterise the study population. Continuous variables will be summarised using mean and standard deviation or median and interquartile range, and categorical variables will be expressed as frequency and percentage. The crude incidence rates for the outcomes of interest will be estimated, reported as cases per 1000 person years with 95% confidence intervals (CIs) derived from a Poisson or negative binomial distribution as appropriate. Time-to-event analysis using Cox proportional hazards models will be used to estimate hazard ratios with 95% CIs. The proportional hazards assumption of the Cox model will be assessed. Potential confounders will be pre-specified based on expert knowledge and available literature, and adjusted for in the model. Using the common protocol, each analysis will be run locally. Estimates for each of the three sites will then be pooled by meta-analysis using a random effects model, and heterogeneity will be estimated using *I*
^2^. All statistical analyses will be performed using either Stata, SAS, or R software.

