#### Subgroup analyses

To explore heterogeneity of exposure effect, subgroup analyses will be conducted by age, sex, LDL-C categories as in the FOURIER trial^4^ (that is <0.5 mmol/l, 0.5 to <1.3 mmol/l, 1.3 to <1.8 mmol/l, 1.8 to <2.6 mmol/l, and ≥2.6 mmol/l), statin adherence prior to follow-up, statin persistence, ethnic group, and prescribed statin dose intensity.

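### Ethnic group is in neither adjustment list, although the protocol links it to statin response and plans a subgroup analysis by it, so within-site confounding of the primary hazard ratio is possible

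*Protocol article*

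**What the plan says.** The Statistical analysis section sets the principle: "Potential confounders will be pre-specified based on expert knowledge and available literature, and adjusted for in the model". The Covariates section carries it out and calls the set a minimum: "A pre-specified minimum list of potential confounders will be adjusted for". Two lists follow.

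- Required, introduced by "The confounders to be adjusted for in each database are as follows": 15 items covering age, sex, diagnoses, smoking, alcohol and co-medication.
- Optional, introduced by "Additional confounders that may be adjusted for subject to data source availability": deprivation index, blood pressure, body mass index and family history of CVD.

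Ethnic group is in neither. Anything beyond the lists has one stated route: "Exploratory modelling will include adjusting for additional confounders that may be available in specific databases".

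Elsewhere ethnic group is prominent. The Introduction states: "Ethnic group, and consequently pharmacogenomics, influences response to statin therapy, particularly for Asians". The Subgroup analyses section includes it among the stratifiers: "statin adherence prior to follow-up, statin persistence, ethnic group, and prescribed statin dose intensity". The Strengths and limitations section presents comparison between ethnic groups as a benefit of the design.

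**The concern.** The exposure is the LDL-C or non-HDL-C level reached 24 months after starting a statin. A factor that changes the response to statins changes the exposure category in which a patient falls. The protocol therefore supplies one of the two links that make a confounder, exposure to ethnic group. If ethnic group is also related to MACE after the listed covariates are taken into account, the comparison of lipid categories within a mixed site is confounded, and the site estimate carries this into the pooled result.

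The protocol sets the bar for inclusion at potential confounding, and ethnic group meets that bar on the protocol's own reasoning. Age and sex are both adjusted for and used as subgroup variables; ethnic group is used only as a subgroup variable, and no reason is given. If the amount of confounding differed by site, it could also add to the between-site heterogeneity that *I*² is meant to describe.

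**Working it through.** **1. The lists.** Required items: age; sex; hypertension; atrial fibrillation; diabetes; dyslipidaemia; obesity; smoking (or nicotine replacement or COPD); alcohol (or liver disease); rheumatoid arthritis or lupus; mental illness; antihypertensives; antidiabetics; antiplatelets; oral anticoagulants. That is 15, without ethnic group. The four optional items do not include it either.

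**2. Which comparison is exposed.** Each Cox model is run locally, and then "Estimates for each of the three sites will then be pooled by meta-analysis using a random effects model". Each site's hazard ratio compares lipid categories among that site's own patients. A difference in ethnic composition between Hong Kong, New Zealand and the UK therefore cannot confound it. Only the ethnic mix within a site can.

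**3. Whether other planned analyses repair it.** The ethnic subgroup analysis gives separate estimates by stratum; it does not change the overall estimate. Models with further confounders are labelled exploratory. The primary hazard ratio remains unadjusted for ethnic group.

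**4. The plan's own figure.** Expected MACE events in the Hong Kong cohort (Feasibility assessment and sample size): 140 000 × 3 years × 10/1000 = 4200, as stated. Adjusting for ethnic group changes none of these inputs. The figure shows only that a few extra parameters are affordable.

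**5. Possible size.** The document gives no ethnic distribution by lipid category for any site and no MACE rate ratio by ethnic group, so all inputs here except the planned hazard ratio of 0.85 are assumptions. For one ethnic group against the rest, let p1 be its share in the low-lipid category, p0 its share in the reference category, and RR its MACE rate ratio conditional on the covariates already in the model. The approximate bias factor is

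(1 + p1(RR − 1)) / (1 + p0(RR − 1)),

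and the estimated hazard ratio is 0.85 times this factor.

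| p0 | p1 | RR | Bias factor | Estimated HR |
|---|---|---|---|---|
| 0.02 | 0.03 | 0.7 | 0.991/0.994 = 0.997 | 0.847 |
| 0.02 | 0.03 | 2.0 | 1.03/1.02 = 1.010 | 0.858 |
| 0.10 | 0.20 | 0.7 | 0.94/0.97 = 0.969 | 0.824 |
| 0.10 | 0.20 | 2.0 | 1.20/1.10 = 1.091 | 0.927 |
| 0.30 | 0.45 | 0.7 | 0.865/0.91 = 0.951 | 0.808 |
| 0.30 | 0.45 | 2.0 | 1.45/1.30 = 1.115 | 0.948 |
| any | any | 1.0 | 1.000 | 0.850 |

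These rows place the group more often in the low-lipid category. Swapping the shares inverts the factor: with p0 = 0.45, p1 = 0.30 and RR = 2.0 it is 1.30/1.45 = 0.897, and the hazard ratio 0.762. The range of about 0.81 to 0.95 is therefore an illustration and not a bound.

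**The case against.** A reader might infer that ethnic group is a known confounder and that the pooled hazard ratio is biased. The document does not support this. It links ethnic group to statin response but nowhere states a link to MACE, and without that link, conditional on the other covariates, there is no confounding. A reader might also infer that the ethnic contrast between the three regions distorts the pooled estimate; fitting within site rules this out.

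Other points on the plan's side:

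- The required list already contains diabetes, hypertension, obesity, smoking and related drugs. Any difference in risk between ethnic groups that runs through these is partly controlled, so a crude rate ratio would overstate the bias. This stands, and is why the rate ratio in the calculation is conditional.
- Availability at every site is inferred from the subgroup plan. The data-source section describes no ethnicity field or its completeness; it says only that the UK source is representative in ethnic group. This may explain why ethnic group is not required in every database. It does not explain its absence from the optional list, which exists for variables that only some sites hold.
- The list is called a minimum, and stratum-specific results could reveal a discrepancy with the overall estimate. Both help interpretation, but neither adjusts the primary estimate.
- The article condenses a fuller plan. But it prints the adjustment set item by item as pre-specified, so the omission lies in what is stated.

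**Conclusion.** The point holds as an inconsistency in a fixed, pre-specified adjustment set. A variable that the protocol itself connects to the exposure, and intends to analyse, is left out of both lists without a reason. The consequence is possible confounding within ethnically mixed sites, in either direction.

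Its size cannot be determined from the document. Under the tabulated assumptions it runs from negligible (0.847 to 0.858 for a small group with nearly equal shares) to material (0.808 to 0.948 for a large group with unequal shares) around a true value of 0.85, and it is nil if the conditional rate ratio is 1. The omission itself is certain; that a bias exists is not shown. The change is worth making because it is cheap and removes a doubt about the primary estimate.

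**What to change.** Add ethnic group, as a categorical variable, to the primary adjustment set at each site where it is recorded. State how missing values are handled: an unknown category, or imputation. The present imputation plan names continuous covariates, so a categorical variable would need its own sentence. Keep the ethnic subgroup analysis. If a site does not hold the variable, say so and report that its estimate is not adjusted for ethnic group. If the authors prefer to leave it out, they should give the reason in the Covariates section.

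The cost is one line in the list and a few parameters per site model, small against the 4200 events expected in Hong Kong alone. The drawbacks are incomplete recording at some sites and, if a site lacks the variable, adjustment sets that differ between the pooled estimates. No stated sample-size figure changes.

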### Eligibility criteria

To be included in the study, each patient must meet the following eligibility criteria:

Have at least one documented baseline lipid test for total cholesterol (TC), HDL-C, and LDL-C within a year prior to index date.Have at least 12 months of clinical records after registration at the practice site (CPRD) or in the database (PREDICT).Have no previous history of atherosclerotic CVD:defined as a hospital or outpatient diagnosis of coronary heart disease (for example, myocardial infarction, ischaemic heart disease, angina, coronary artery bypass graft, percutaneous intervention), cerebrovascular disease (stroke or transient ischaemic attack), or peripheral artery disease (PAD), prior to index date; ordiagnosis of heart failure, chronic kidney disease, or diabetes with chronic kidney disease, due to their equivalent level of risk as people with established CVD, prior to index date; ora prescribing or dispensing of at least one prescription for nitrates, other antianginal drugs, peripheral vasodilators, loop diuretics, or metolazone within a year prior to index date.Be aged ≥18 years on index date.Have at least two additional statin prescriptions 1 year following index date.Have at least one documented follow-up lipid test for TC, HDL-C, and LDL-C in the year prior to the start of follow-up.

Participants who die or experience MACE before the start of follow-up will be excluded. Each participant who meets the study eligibility criteria will be entered once for analysis; duplicate entries will be removed.

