### Exposures

Serum concentrations of LDL-C and non-HDL-C 24 months after initiating a statin are the primary exposures of interest (Figure 1). The latest lipid test measurement for patients with multiple records for lipid tests during the exposure assessment window will be selected. If non-HDL-C has not been reported, it will be calculated as TC − HDL-C.^6^ This timeframe after statin initiation was selected as this is when a measurable benefit in reducing cardiovascular events from statin treatment occurred in randomised controlled trials.^22,23^ Furthermore, the 24-month time point ensures most follow-up cholesterol measures are captured in the electronic health records within each database.^12^

Patients will be categorised into four exposure groups according to lipid concentrations based on specific treatment targets recommended in clinical practice guidelines.^6,24^

For LDL-C:

<1.4 mmol/l (<55 mg/dl)≥1.4 to <1.8 mmol/l (≥55 to <70 mg/dl)≥1.8 to <2.6 mmol/l (≥70 to <100 mg/dl)≥2.6 mmol/l (≥100 mg/dl).

For non-HDL-C:

<2.2 mmol/l (<85 mg/dl)≥2.2 to <2.6 mmol/l (≥85 to <100 mg/dl)≥2.6 to <3.4 mmol/l (≥100 to <130 mg/dl)≥3.4 mmol/l (≥130 mg/dl).

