### Statistical analysis plan

#### Data cleaning and validation

Variable definitions will be harmonised among the three sites through consensus discussion. A common analysis protocol will be created, with the aim of standardising variables in terms of measurement units and timing of measurements. For each database, the most appropriate set of operational definitions will be applied, while considering any unique aspects of the database. Then work to standardise these definitions between each database will be undertaken. Outliers for continuous exposures and covariates will be explored. Implausible values, such as negative lipid concentrations, will be removed. The distribution of continuous variables will be compared with the known distribution from a representative population survey. Multiple imputation by chained equations will be used to address missing data of continuous covariates (for example, blood pressure) and estimates pooled according to Rubin’s rules. Baseline and follow-up lipid tests will not be imputed (see eligibility criteria).

Sites will manage data access and data curation as per local policies and guidelines. Electronic health data will be stored securely and analysed locally. Anonymised patient-level data will not be shared between sites.

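### The main model commits to no baseline lipid concentration, although every patient has one, so the hazard ratios for achieved LDL-C and non-HDL-C mix achieved level with starting level.

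*Protocol article*

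**What the plan says.** All references are to the protocol article.

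- **Exposure (Exposures).** "Serum concentrations of LDL-C and non-HDL-C 24 months after initiating a statin are the primary exposures of interest". Each is cut into four groups at guideline targets. For unreported non-HDL-C: "If non-HDL-C has not been reported, it will be calculated as TC − HDL-C".
- **Baseline lipids (Eligibility criteria).** Each patient must "Have at least one documented baseline lipid test for total cholesterol (TC), HDL-C, and LDL-C within a year prior to index date". Data cleaning and validation excludes baseline and follow-up lipids from imputation and refers back to eligibility.
- **Mandatory adjustment (Covariates).** "The confounders to be adjusted for in each database are as follows", followed by 15 items: age, sex, diagnoses, smoking, alcohol and prescriptions. The only lipid item is a diagnosis of dyslipidaemia.
- **Optional adjustment (Covariates).** "Additional confounders that may be adjusted for subject to data source availability": deprivation, baseline blood pressure, baseline body mass index and family history.
- **Other routes (Covariates).** The mandatory list is called a minimum, and "Exploratory modelling will include adjusting for additional confounders that may be available in specific databases".
- **Subgroup and Sensitivity analyses.** Neither section describes an analysis by baseline lipid level or by change from baseline.
- **Question (Introduction).** The article states that "Atherogenic lipoproteins (LDL-C and non-HDL-C) are well-established risk factors for atherosclerotic CVD" and asks whether reaching a specific lipid target on a statin corresponds to fewer cardiovascular events.

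**The concern.** A patient's LDL-C at 24 months is the starting level reduced by the response to treatment. The starting level comes before the exposure and partly determines it. By the article's own account, these lipids are also risk factors for the outcome. That makes baseline level a common cause of exposure and outcome, and here it is measured in everyone.

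Without it, a comparison of low with high achieved groups also compares people who started low with people who started high. The bias can run either way. Higher past lipid exposure would make low achieved levels look protective beyond any real effect. If patients with a low starting level were given a statin because of other, poorly captured risk, the baseline association could be inverse and a real benefit would be masked.

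A yes/no dyslipidaemia code among people who all start a statin leaves most of the variation in level uncontrolled. Pooling the sites does not help, because the same term is missing at each.

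**Working it through.** **1. The plan's own figure.** Feasibility assessment and sample size gives 140 000 CDARS patients, at least 3 years and 10 events per 1000 person years:

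140 000 × 3 × 10/1000 = 4200 events, as stated.

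This figure is not in dispute. It is used in step 4.

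**2. Size of the confounding.** The article gives no lipid distributions and names no reference category, so every input here is an assumption:

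- baseline LDL-C *B*: mean 3.8, SD 0.9 mmol/l
- achieved LDL-C *F*: mean 2.4, SD 0.7 mmol/l
- *B* and *F* bivariate normal with correlation *r* from 0.2 to 0.7
- hazard ratio per mmol/l of baseline, given achieved level: 1.1 to 1.3, or 0.9 for an inverse association
- no true effect of achieved level
- contrast <1.4 versus ≥2.6 mmol/l

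Apparent ratio = mean of exp[β(*B* − 3.8)] among *F* < 1.4, divided by the same mean among *F* ≥ 2.6, with β = ln(baseline HR). Results from 2 000 000 simulated patients:

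| *r* | Mean *B*, *F* < 1.4 | Mean *B*, *F* ≥ 2.6 | HR 0.9 | HR 1.1 | HR 1.2 | HR 1.3 |
|---|---|---|---|---|---|---|
| 0.2 | 3.46 | 3.98 | 1.056 | 0.952 | 0.910 | 0.873 |
| 0.3 | 3.29 | 4.07 | 1.085 | 0.929 | 0.869 | 0.816 |
| 0.5 | 2.96 | 4.25 | 1.145 | 0.884 | 0.790 | 0.713 |
| 0.7 | 2.62 | 4.42 | 1.209 | 0.842 | 0.719 | 0.621 |

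Hand check at *r* = 0.3, HR 1.2: exp[ln(1.2) × (3.29 − 4.07)] = exp(0.182 × −0.78) = 0.87, which agrees.

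If the true ratio were 0.85, that cell would show 0.85 × 0.869 ≈ 0.74, and the inverse case at the same *r* would show 0.85 × 1.085 ≈ 0.92.

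The illustration leaves out the dyslipidaemia code and the other listed covariates. These would absorb part of the bias.

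**3. A second construction.** Here achieved level is baseline times (1 − response), with a log hazard ratio of 0.15 per mmol/l of baseline and again no effect of achieved level. A response SD of 15% gives an apparent ratio of about 0.75; an SD of 25% gives about 0.85. The more variable the response, the lower the correlation and the smaller the bias.

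**4. Precision cost of adjusting.** Schoenfeld's formula for HR 0.85, two-sided 0.05 and power 0.80 is

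events = (1.96 + 0.84)² / [p(1 − p)(ln 0.85)²].

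Equal groups need 1189 events. If the smaller group holds 10% of patients (assumed), 3302 are needed. Dividing by (1 − *r*²) allows for the correlation with baseline:

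- equal groups: 1189/0.96 = 1239 at *r* = 0.2, up to 1189/0.51 = 2332 at *r* = 0.7; both are below 4200
- 10% group: 3302/0.96 = 3440, up to 3302/0.51 = 6475; at *r* = 0.5 it is 3302/0.75 = 4403, just above the 4200 from CDARS alone, before the other two databases are pooled

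This treats the group contrast as fully correlated with baseline, so it is likely to overstate the cost at high *r*. A simulation with categorical exposure put the rise in the standard error of the log hazard ratio at about 5% to 17%.

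**The case against.** **The stated objective is an association.** The second objective concerns the association between 24-month concentrations and MACE, and the groups follow absolute guideline targets. A model without baseline answers that descriptively. This stands. A reader might infer that the study cannot answer its question; that goes too far. The estimate is biased to an unknown degree for the question about achieving a target, but it is not uninformative.

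**The list is a minimum.** Exploratory models may add confounders, and Statistical analysis says confounders are chosen from expert knowledge and literature. So it cannot be said that no analysis will ever use baseline lipids. What stands is that the main model does not commit to them, and that unnamed, database-specific additions are not harmonised across sites.

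**The size depends on the inputs.** A reader might infer that the false effect must exceed the planned hazard ratio of 0.85. The documents do not support this. Entry requires only two further statin prescriptions in the first year, and the article stresses variable response and plans subgroups by adherence and persistence. All of this favours a lower correlation and a smaller bias. Nor is <1.4 versus ≥2.6 mmol/l named as the primary contrast.

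**Adjustment changes the contrast.** With baseline held fixed, differences in achieved level come mostly from response, adherence and dose. Adherence and dose intensity are subgroup factors, not covariates, so confounding by adherence may become more prominent. This stands and belongs in the fix.

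**Conclusion.** The omission is in the article's own text: a set specified for every database, with no baseline lipid concentration, beside eligibility rules that guarantee the measurement. It is not a detail left to a fuller plan. As written, the main hazard ratios mix achieved with starting level and are biased for the question about achieving a target.

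Under the stated assumptions and a null effect, the apparent ratio for <1.4 versus ≥2.6 mmol/l runs from 0.95 (*r* 0.2, baseline HR 1.1) to 0.62 (*r* 0.7, baseline HR 1.3), or from 1.06 to 1.21 with an inverse baseline association. The planned 0.85 lies within the first range, so the bias could be as large as the effect sought. Neither its actual size nor its direction can be derived from the documents.

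**What to change.** Under Covariates, add to the mandatory set at all three sites:

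- baseline LDL-C, as a continuous term, in the LDL-C models
- baseline non-HDL-C (total cholesterol minus HDL-C), as a continuous term, in the non-HDL-C models

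Report the model without baseline alongside. State that the adjusted contrast compares achieved levels among patients with the same starting level, and so also reflects degree of reduction. Name the reference category.

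Cost: a short addition to the covariate list and no loss of patients, because eligibility already requires the data. Confidence intervals will be somewhat wider. Data will be sparse for patients who start high and reach the lowest group. Confounding by adherence and treatment indication will remain and should be acknowledged.

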### Outcomes and follow-up

The primary outcome of interest is MACE, defined as a diagnosis of either coronary heart disease, stroke, or cardiovascular death. Secondary outcomes include all-cause mortality and the individual components of the composite MACE outcome. Follow-up will begin after the end of the exposure assessment window (24 months after prescribing or dispensing of the first statin prescription) and will end at the earliest of outcome of interest, death, disenrollment or transfer from primary care practice, or end of the analysis period (31 December 2017).

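### The minimum confounder list omits cancer and no analysis lags the start of follow-up, so all-cause mortality in the lowest LDL-C group may be biased upward by pre-existing serious illness

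*Protocol article*

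**What the plan says.** All references are to the protocol article.

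- **Covariates.** "A pre-specified minimum list of potential confounders will be adjusted for". The list itself is introduced by "The confounders to be adjusted for in each database are as follows" and has 15 items: age, sex, cardiometabolic diagnoses, smoking (with COPD as an alternative marker), alcohol use (with chronic liver disease as an alternative), rheumatoid arthritis or lupus, mental illness, and four drug groups. Cancer, frailty, weight loss and a general comorbidity index are absent. Beyond the list, "Exploratory modelling will include adjusting for additional confounders that may be available in specific databases". The four additions named are deprivation, blood pressure, body mass index and family history of CVD.
- **Eligibility criteria.** Atherosclerotic CVD, heart failure, chronic kidney disease and recent use of certain cardiac drugs exclude a patient. Cancer does not. The follow-up test requirement reads "Have at least one documented follow-up lipid test for TC, HDL-C, and LDL-C in the year prior to the start of follow-up". Also, "Participants who die or experience MACE before the start of follow-up will be excluded".
- **Exposures.** "The latest lipid test measurement for patients with multiple records for lipid tests during the exposure assessment window will be selected".
- **Outcomes and follow-up.** "Follow-up will begin after the end of the exposure assessment window", at 24 months. MACE is the primary outcome; all-cause mortality is secondary. Death ends follow-up.
- **Sensitivity analyses.** The 3-month version assesses lipids on days 30-90 and follows from day 91. The 12-month version uses days 1-365 and follows from day 366.

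**The concern.** Advanced or developing serious illness, with cancer the plainest case, can depress cholesterol and raise the risk of death soon afterwards. Patients in that state collect in the lowest LDL-C category for reasons unrelated to statin response. Three choices in the article work together here. Taking the latest test brings the exposure as near as possible to the start of follow-up. Counting events from the end of the window lets deaths from illness already present at the test enter the comparison. The required adjustment set has no term for the illness.

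The bias falls at the low end of the LDL-C range, which is where the Introduction places one of its open questions: "It is also unknown whether there is a lipid level threshold, below which no added clinical benefit is obtained". A mortality hazard ratio pushed towards or above 1 in the lowest group could be read as loss of benefit, or as harm, at low LDL-C. Sample size gives no protection, because this is bias and not imprecision.

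**Working it through.** **1. The plan's own figure.** Feasibility assessment and sample size gives 140 000 CDARS patients, at least 3 years of follow-up and 10 MACE per 1000 person-years: 140 000 × 3 × 10/1000 = 4200 events, as stated. This figure is used only to cost the fix.

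**2. Is there a gap between exposure and event counting?** In the main analysis the window ends at 24 months and follow-up begins then. In the sensitivity analyses day 90 is followed by day 91, and day 365 by day 366. The test and the start of counting move together, so no version imposes a lag. A patient tested early in the final year has an incidental gap, but the rule that takes the latest test does not guarantee one.

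**3. Size of the bias for all-cause mortality.** For an unmeasured binary condition,

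bias factor = [1 + pL(k − 1)] / [1 + pH(k − 1)],

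where pL and pH are the prevalences of serious illness in the lowest and the other LDL-C groups, and k is its hazard ratio for death. All three are assumptions: pL 2-5%, pH 1%, k 5-10. The 0.85 is borrowed from the sample-size paragraph, where it is the planned hazard ratio, and serves here only as an illustration for mortality.

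| pL | pH | k | Bias factor | 0.85 appears as |
|---|---|---|---|---|
| 2% | 1% | 5 | 1.08/1.04 = 1.04 | 0.88 |
| 2% | 1% | 10 | 1.18/1.09 = 1.08 | 0.92 |
| 5% | 1% | 5 | 1.20/1.04 = 1.15 | 0.98 |
| 5% | 1% | 10 | 1.45/1.09 = 1.33 | 1.13 |

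**4. What would hide a 0.85 completely?** A bias factor of 1/0.85 = 1.18. Solving for pL with pH = 1%: for k = 5, (1.1765 × 1.04 − 1)/4 = 5.6%; for k = 10, (1.1765 × 1.09 − 1)/9 = 3.1%.

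**5. The same formula for MACE.** A cancer death is not a MACE event, so a much smaller k applies; 1.5 to 2 is assumed. With the prevalences above, the factor runs from 1.01/1.005 = 1.005 to 1.05/1.01 = 1.04, and 0.85 appears as 0.85 to 0.88. With larger assumed prevalences (6% against 2%, or 10% against 3%) it appears as 0.87 to 0.91. The association is weakened, not reversed.

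**6. Limits of the formula.** It makes no allowance for covariates already in the model, such as age and smoking or COPD, which would absorb part of the bias. It also describes the start of follow-up: as ill patients die, the imbalance shrinks, so an average over several years would be smaller.

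**The case against.** The strongest case on the other side has five parts.

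- **The list is a floor.** A reader might infer from its wording that the list is closed. It is not: the article calls it a minimum and allows additions. What remains is that additions are described as exploratory, depend on the database and do not name cancer, so nothing commits the pooled estimates to this adjustment.
- **The objectives concern MACE.** A reader might infer that the study's main answer is at risk of a false threshold or apparent harm. The documents do not support that. Both objectives are about MACE, non-cardiovascular deaths only end follow-up, and step 5 shows attenuation only. The point belongs mainly to one secondary outcome.
- **The design already removes some ill patients.** They must survive 24 months without MACE, have at least two further statin prescriptions in the first year, and have no prior heart failure or chronic kidney disease. COPD, liver disease and autoimmune disease are partly covered. This reduces the problem, but does not reach illness that arises close to the last lipid test.
- **The magnitude is assumed.** This is correct. The range runs from trivial to a reversal, nothing in the documents favours either end, and no mortality effect is planned.
- **A lagged run may sit in a fuller plan.** It may. The point rests on what the article does print: the required list, the windows and the sensitivity analyses, which together leave the gap.

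**Conclusion.** The point holds in a limited form. As written, the required adjustment set and the start of follow-up leave reverse causation at low LDL-C uncontrolled, chiefly for all-cause mortality. Under the stated assumptions the mortality hazard ratio for the lowest group is inflated by 4% to 33%. These are illustrative bounds, not an estimate, and probably lean high for the reasons in step 6. For MACE the distortion is likely to be small. The change is worth making because it is cheap and because the affected group is the one on which any statement about very low LDL-C will depend.

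**What to change.** 1. In Covariates, add a diagnosis of cancer before the start of follow-up to the minimum list for every database.
2. In Sensitivity analyses, add a run that leaves out the first 12 months of follow-up (events and person-time), mainly for all-cause mortality and also for MACE.

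The two are complementary: the covariate deals with diagnosed cancer, and the lag deals with illness not yet recorded at the lipid test.

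The cost is one more harmonised code list per database and one extra run. The article does not describe cancer coding in the three sources, so its completeness should be checked first. The lagged run loses the first year's events: in CDARS, 140 000 × 2 × 10/1000 = 2800 MACE events remain of 4200 over 3 years. The main analysis keeps all its events, and no figure stated in the article changes.
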